**Table S3. Factors associated with pneumococcal density in the control group**

| Variable                          | Change in
log10copies/μl | Standard
Error | P value# |
|------------------------------------------|-------------------------------------|---------------------------|----------------------------|
| Asymptomatic respiratory virus at day 0  | +0.135                              | 0.164                     | 0.41                       |
| Day 7 ( vs day 0)                        | +0.022                              | 0.130                     | 0.86                       |
| Day 21 (vs day 0)                        | +0.232                              | 0.130                     | 0.076                      |
| Recruitment in 2018 (vs 2017)            | +0.402                              | 0.166                     | 0.018                      |
| Age (in months)                          | +0.135                              | 0.164                     | 0.45                       |
| Household cooking indoors (vs outdoors)^ | -0.263                              | 0.277                     | 0.34                       |

#P values for factors associated with *S. pneumoniae* density are derived from a generalized linear mixed-effect model. Reference levels for each variable are given within brackets. ^Cooking inside (under a roof) compared to cooking using an indoor kitchen. Note 99% of children lived in households where wood/charcoal was primary fuel used to cook regardless of location of cooking.

**Table S4. Factors associated with pneumococcal density in children recruited in 2017**

| Variable                          | Change in
log10copies/μl | Standard
Error | Degrees
of
freedom | P value# |
|------------------------------------------|-------------------------------------|---------------------------|-----------------------------------|----------------------------|
| LAIV receipt at Day 0 (vs control)       | +0.323                              | 0.127                     | 168                               | 0.012                      |
| Asymptomatic respiratory virus at day 0  | +0.140                              | 0.130                     | 168                               | 0.28                       |
| Day 7 (vs day 0)                         | +0.025                              | 0.112                     | 345                               | 0.82                       |
| Day 21 (vs day 0)                        | -0.065                              | 0.112                     | 345                               | 0.56                       |
| Age (in months)                          | -0.014                              | 0.007                     | 169                               | 0.034                      |
| Household cooking indoors (vs outdoors)^ | -0.160                              | 0.246                     | 168                               | 0.52                       |

#P values for factors associated with *S. pneumoniae* density are derived from a generalized linear mixed-effect model. Reference levels for each variable are given within brackets. ^Cooking inside (under a roof) compared to cooking using an indoor kitchen. Note 99% of children lived in households where wood/charcoal was primary fuel used to cook regardless of location of cooking.

**Table S5. Factors associated with pneumococcal density in children recruited in 2018**

| Variable                                      | Change in
log10copies/μl | Standard
Error | P value # |
|------------------------------------------------------|-------------------------------------|---------------------------|-----------------------------|
| LAIV receipt at Day 0 (vs control)                   | -0.139                              | 0.155                     | 0.37                        |
| Asymptomatic respiratory virus at day 0              | +0.346                              | 0.149                     | 0.022                       |
| Day 7 (vs day 0)                                     | +0.295                              | 0.116                     | 0.012                       |
| Day 21 (vs day 0)                                    | +0.685                              | 0.116                     | <0.0001                     |
| Age (in months)                                      | -0.016                              | 0.008                     | 0.042                       |
| Household cooking indoors (vs outdoors) ^ | -0.359                              | 0.201                     | 0.078                       |

#P values for factors associated with *S. pneumoniae* density are derived from a generalized linear mixed-effect model. Reference levels for each variable are given within brackets. ^Cooking inside (under a roof) compared to cooking using an indoor kitchen. Note 99% of children lived in households where wood/charcoal was primary fuel used to cook regardless of location of cooking.

**Table S6. D7 to D21 change in pneumococcal density in children without asymptomatic respiratory virus at day 0 in the control group**

| Variable                                      | Change in
log10copies/μl | Standard
Error | P value # |
|------------------------------------------------------|-------------------------------------|---------------------------|-----------------------------|
| Day 21 (vs day 7)                                    | +0.311                              | 0.155                     | 0.0501                      |
| Age (in months)                                      | -0.009                              | 0.013                     | 0.48                        |
| Recruitment in 2018 (vs 2017)                        | +0.573                              | 0.232                     | 0.017                       |
| Household cooking indoors (vs outdoors) ^ | -0.146                              | 0.363                     | 0.69                        |

#P values for factors associated with *S. pneumoniae* density are derived from a generalized linear mixed-effect model. Reference levels for each variable are given within brackets. ^Cooking inside (under a roof) compared to cooking using an indoor kitchen. Note 99% of children lived in households where wood/charcoal was primary fuel used to cook regardless of location of cooking.

**Table S7. Viral infections acquired between baseline (day 0) and day 7 in the control group.**

|                                            | 2017
n=48 | 2018
n=42 | P value# |
|--------------------------------------------|----------------------|----------------------|----------------------------|
| Day 7 respiratory viral infections* | 10 (20·8%)    | 17 (40·5%)    | 0·07                |
| Adenovirus                                 | 0 (0·0%)             | 2 (11·8%)            |                            |
| Seasonal coronaviruses (sCoV)              | 1 (10·0%)            | 3 (17·6%)            |                            |
| Parainfluenza 1                            | 0 (0·0%)             | 1 (5·9%)             |                            |
| Influenza B & Rhinovirus                   | 0 (0·0%)             | 2 (11·8%)            |                            |
| Rhinovirus                                 | 8 (80·0%)            | 7 (41·2%)            |                            |
| Rhinovirus & Adenovirus                    | 1 (10·0%)            | 1 (5·9%)             |                            |
| Rhinovirus & sCoV                          | 0 (0·0%)             | 1 (5·9%)             |                            |

\*Shown are new viruses detected at day 7 that were not present at baseline (day 0). Samples where the same virus was detected at day 7 that was present at baseline are not included (n=11). #P value derived from Fisher's exact test comparing the presence of any respiratory virus across years.

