#### **86**    Obtaining nasopharyngeal samples

A single paediatric Copan flocked nasopharyngeal swab will be obtained from children at the time points specified in the schedule of events. Detailed practical instructions regarding the collection of NPS will be outlined in the relevant study specific procedure.

Once obtained, NPS will immediately be placed aseptically into a vial of RNaProtect® cell reagent, the swab snapped as per manufacturer's recommendations and the lid of the vial closed immediately.

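### Table S7 appears to leave 11 control children out of its acquisition rates because of their day 7 result, and the 2017 v 2018 P value then depends on their unreported split by year

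*Combined protocol and SAP*

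**What the plan says.** Table S7, in the appendix to the combined document, concerns respiratory viruses that control children picked up between day 0 and day 7, by recruitment year. It prints 10 (20.8%) of 48 in 2017 and 17 (40.5%) of 42 in 2018, with P = 0.07.

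The footnote defines what is counted: "Shown are new viruses detected at day 7 that were not present at baseline (day 0". It adds: "Samples where the same virus was detected at day 7 that was present at baseline are not included (n=11". On the test it says: "P value derived from Fisher's exact test comparing the presence of any respiratory virus across years".

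The footnote does not say whether the 11 are outside the denominators or only left out of the event counts. It gives neither their split by year nor whether any of them also carried a second, new virus. Tables S10 and S11 give the control group as 108 children. Protocol section 86 provides for one swab per visit ("A single paediatric Copan flocked nasopharyngeal swab will be obtained from children at the time points specified in the schedule of events"), so 11 samples at day 7 are 11 children.

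**The concern.** For a rate of new acquisition, the denominator should be fixed by what is known at day 0. The exclusion rule in the footnote uses the day 7 swab. Take two children who both carry rhinovirus at day 0 and acquire nothing else. If one clears the virus by day 7, that child counts as a non-event. If the other still carries it, that child is left out, although neither acquired a virus. Conversely, a child with a persistent virus plus a new one is a true event who would also be lost.

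What is at stake is the comparison between years. Pneumococcal density results differ by year: Table S2 has a group-by-year interaction with P = 0.016, and the LAIV coefficient is +0.323 in Table S4 (2017) and -0.139 in Table S5 (2018). A reader may turn to Table S7 for whether background virus acquisition also differed between the years. That answer should not depend on an undisclosed split of 11 children.

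**Working it through.** **Inputs.** Table S7: 10/48, 17/42, P = 0.07, 11 samples not included. Tables S10 and S11: 108 controls. Table S4: 168 degrees of freedom for most between-child terms.

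**1. Reproduce the printed figures.** 10/48 = 20.8% and 17/42 = 40.5%, as printed. The virus rows sum to 10 and 17. The usual two-sided Fisher exact test on 10/48 v 17/42 gives P = 0.064, which rounds to 0.06. Doubling the one-sided Fisher P gives 2 × 0.0359 = 0.072, which rounds to the printed 0.07.

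**2. Are the 11 outside the denominators?** 48 + 42 = 90, and 90 + 11 = 101, leaving 108 - 101 = 7 controls unexplained. If the 11 are inside the 90, 108 - 90 = 18 are unexplained. Both are possible. The wording favours the first: the preceding sentence already limits the counts to new viruses, so a further statement that samples are left out reads as removal of children.

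**3. Put the 11 back as non-events.** Overall: 27/90 = 30.0% becomes 27/101 = 26.7%. The ratio is 101/90 = 1.12, a relative overstatement of 12%. By year, with two-sided Fisher P:

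| Of the 11, in 2017 / 2018 | 2017 | 2018 | P |
|---|---|---|---|
| 0 / 11 | 10/48 = 20.8% | 17/53 = 32.1% | 0.262 |
| 3 / 8 | 10/51 = 19.6% | 17/50 = 34.0% | 0.120 |
| 5 / 6 | 10/53 = 18.9% | 17/48 = 35.4% | 0.074 |
| 6 / 5 | 10/54 = 18.5% | 17/47 = 36.2% | 0.070 |
| 7 / 4 | 10/55 = 18.2% | 17/46 = 37.0% | 0.043 |
| 10 / 1 | 10/58 = 17.2% | 17/43 = 39.5% | 0.022 |
| 11 / 0 | 10/59 = 16.9% | 17/42 = 40.5% | 0.012 |

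P is below 0.05 when 7 or more of the 11 are 2017 children.

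**4. Which splits are plausible?** This step is an assumption. Table S4's 168 degrees of freedom plus five between-child coefficients (intercept, LAIV, baseline virus, age, cooking) suggest about 173 children in 2017. One third as controls is 173/3 ≈ 58, leaving 108 - 58 = 50 in 2018. Then at most 58 - 48 = 10 of the 11 fall in 2017 and at most 50 - 42 = 8 in 2018. The 2017 share is therefore 3 to 10, and P runs from 0.12 to 0.022.

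**5. If some of the 11 also had a new virus.** With 3 such children the overall rate is 30/101 = 29.7%; with 4 it is 31/101 = 30.7%, above the printed 30.0%. If all 11 had one, P runs from 0.001 to 0.68 depending on the split.

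**The case against.** The strongest reply is that the footnote may mean only that persistent viruses were not counted as new. The 11 would then already be non-events within the 90, which is the correct handling, and the proportions would need no change. The 18 controls outside the 90 could be missed visits or missing results: section 58 of the protocol says samples for a missed visit window are not collected. That 101 fits within 108 is weak evidence, since any total up to 108 would fit. This objection stands as far as it goes: removal from the denominators is likely, not proven.

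The printed P value does not decide between the readings. The value 0.07 is matched by a doubled one-sided Fisher test on the printed counts, but also by the usual two-sided test with the 11 restored 5/6 or 6/5 (0.074, 0.070). In the second case the P value would already include the 11 while the percentages would not, and the table would be internally inconsistent.

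A reader might infer that the rates are certainly overstated, or that the year difference could be anything from clearly significant to clearly absent. The documents support neither. The direction reverses if 4 or more of the 11 had a new virus. The extremes of 0.012 and 0.26 need 59 controls in 2017 or 53 in 2018, which the group sizes inferred above would not allow, although that inference is approximate.

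Finally, the table is descriptive. Section 19 of the protocol lists respiratory viruses at vaccination as an exploratory endpoint, not acquisition by day 7, and the density models in Tables S2 to S5 adjust for baseline virus only.

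**Conclusion.** The point holds conditionally. On the plainer reading of the footnote, Table S7 excludes children on their day 7 result. If the 11 are outside the 90 and none had a new virus, acquisition is 26.7% and not 30.0%; the printed rate is too high as long as at most 3 of them had a new virus. With the 11 as non-events, the between-year P lies between 0.012 and 0.26 over all splits, and about 0.02 to 0.12 under the assumed group sizes. Both ranges cross 0.05. The rate in 2018 exceeds 2017 in every such split, so the direction of the year difference is not in doubt under that assumption; its strength is.

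If the 11 are already non-events among the 90, the proportions are right. Under either reading the table needs clarification: the printed 0.07 is not the usual two-sided Fisher result on the printed counts (0.064), and the footnote describes the test as covering any respiratory virus while the row counts only new ones. The effect is confined to the between-year comparison of virus acquisition in controls; no primary result changes.

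**What to change.** - Take as denominator every control child with paired day 0 and day 7 virus results, including the 11.
- Count a child as an event if any virus is present at day 7 that was absent at day 0, whether or not another virus persisted.
- Recompute the percentages and the two-sided Fisher P from those same counts, name the variant used, and make the footnote's description of the test match the row tested.
- State the split of the 11 by year, how many had a new virus, and why any remaining controls of the 108 are absent.
- Make any restricted analysis by day 0 status only, for example children who were virus-negative at day 0.

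The cost is re-tabulating data already held. The P value may move either way.

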**Table S8. Association between day 7 LAIV shedding and day 7 pneumococcal density.**

| Variable                             | Change in
log10copies/μl | Standard
Error | P value |
|---------------------------------------------|-------------------------------------|---------------------------|----------------|
| Day 7 high LAIV shedding (vs low shedding)* | +0·380                              | 0·167                     | 0·024          |
| Asymptomatic respiratory virus at day 0     | +0·442                              | 0·170                     | 0·0099         |
| Recruitment in 2018 (vs 2017)               | -0·259                              | 0·162                     | 0·11           |
| Age (in months)                             | -0·017                              | 0·009                     | 0·059          |
| Household cooking indoors (vs outdoors)^    | +0·006                              | 0·257                     | 0·98           |

\*high LAIV shedding was defined as having at least one LAIV strain (of three measured) with a RT-PCR cycle threshold (Ct) value equal to or lower than the median Ct value of all LAIV RT-PCR data at day 7. Note lower Ct values denote higher amount of virus. ^Cooking inside (under a roof) compared to cooking using an indoor kitchen. Note 99% of children lived in households where wood/charcoal was primary fuel used to cook regardless of location of cooking.

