**Table S9. Association between day 2 LAIV shedding and day 7 pneumococcal density.**

| Variable                             | Change in
log10copies/μl | Standard
Error | P value |
|---------------------------------------------|-------------------------------------|---------------------------|----------------|
| Day 2 high LAIV shedding (vs low shedding)* | +0.036                              | 0.167                     | 0.83           |
| Asymptomatic respiratory virus at day 0     | +0.42                               | 0.172                     | 0.015          |
| Recruitment in 2018 (vs 2017)               | -0.233                              | 0.166                     | 0.16           |
| Age (in months)                             | -0.023                              | 0.009                     | 0.013          |
| Household cooking indoors (vs outdoors)^    | +0.011                              | 0.260                     | 0.97           |

\*high LAIV shedding was defined as having at least one LAIV strain (of three measured) with a RT-PCR cycle threshold (Ct) value equal to or lower than the median Ct value of all LAIV RT-PCR data at day 7. Note lower Ct values denote higher amount of virus. ^Cooking inside (under a roof) compared to cooking using an indoor kitchen. Note 99% of children lived in households where wood/charcoal was primary fuel used to cook regardless of location of cooking.

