## **91 Nasopharyngeal swabs**

NPS vials will be placed on an ice block and transported to the laboratory within 3 hours for processing and storage within 4 hours. Samples will be processed in the research immunology laboratory according to study specific procedures, with the 1ml sample being split into five equal aliquots of 200ul and stored at -70 °C.

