## **97 Influenza-specific IgA and IgG**

An aliquot of NPS collected material and oral fluid will be shipped frozen on dry ice to RIVM laboratories in the Netherlands, where anti-influenza IgA will be measured using a protein microarray [70]. This fluorescence-based assay utilizes very small amounts of material and preliminary data shows very good correlation with nasal fluid anti-influenza IgA estimated by more traditional indirect enzyme-linked immunosorbent assay (ELISA) methods ([name],

[name], unpublished). In addition, indirect ELISA assays to determine anti-influenza IgA and IgG from oral fluid, where more material is available will be set up and performed at the MRC Gambia immunology research laboratory. Total IgA and IgG will also be estimated in NPS material and oral fluid (by ELISA) and influenza-specific IgA and IgG expressed as a ratio of total IgA and IgG respectively. Further exploratory assays may be carried out after optimization to obtain a more functional output of anti-influenza activity in mucosal secretions.

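### Table S8 relates LAIV shedding to pneumococcal density from the same day 7 swab, with no stated yield correction and no day 0 density, so its +0.380 may be biased upward

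*Combined protocol and SAP*

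**What the plan says.** Section 86 of the protocol provides for one swab per visit: "A single paediatric Copan flocked nasopharyngeal swab will be obtained from children at the time points specified in the schedule of events". Section 91 then has it divided, "with the 1ml sample being split into five equal aliquots of 200ul". Table 3 assigns the day 7 swab both to microbiome work and to the RT-PCR for vaccine-virus shedding. With only one swab per visit, a day 7 pneumococcal qPCR result must come from that swab as well.

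Table S8 in the appendix is titled "Association between day 7 LAIV shedding and day 7 pneumococcal density". Its shedding row reads "Day 7 high LAIV shedding (vs low shedding)* | +0·380" in log10 copies/μl, with SE 0.167 and P = 0.024. Its footnote defines high shedding this way: "having at least one LAIV strain (of three measured) with a RT-PCR cycle threshold (Ct) value equal to or lower than the median Ct". The median is taken over the day 7 results for the vaccine strains. The other terms listed are respiratory virus at day 0, recruitment year, age and cooking location.

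Table S9, "Association between day 2 LAIV shedding and day 7 pneumococcal density", has the same layout. Its row is "Day 2 high LAIV shedding (vs low shedding)* | +0.036", with SE 0.167 and P = 0.83. Its footnote defines high day 2 shedding by the median Ct at day 7.

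For antibody from swab and oral fluid, section 97 plans "influenza-specific IgA and IgG expressed as a ratio of total IgA and IgG respectively". For bacteria, sections 126 and 128 plan relative as well as absolute abundance of the pneumococcal OTU. Neither kind of scaling is stated for Table S8.

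**The concern.** A swab that picks up more material lowers the viral Ct and raises the pneumococcal copies/μl at the same time. If collection varies between children, some positive association appears even when virus and pneumococcus are unrelated. The direction is known: the artefact can only add to the estimate.

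A second route is prior carriage. Children with dense carriage before vaccination may shed more virus and will tend to have dense carriage at day 7. The S8 outcome is a single time point, so only a day 0 density term would address this, and none is listed, although density before vaccination is part of a primary endpoint.

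What is at stake is how a 2.4-fold difference is read. Pneumococcal burden after LAIV belongs to a primary objective, and a reader could take S8 as support for vaccine replication raising it.

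**Working it through.** **Inputs from the documents.** Table S8: estimate 0.380, SE 0.167, P = 0.024. Table S9: 0.036, SE 0.167, P = 0.83. Table S10: 213 LAIV recipients, an upper bound because S8 gives no n.

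**1. Reproducing the tables.** 0.380 / 0.167 = 2.275. With 150 to 205 degrees of freedom (assumed), P = 0.0243 to 0.0239, which rounds to the stated 0.024. The 95% CI is 0.380 ± 1.96 × 0.167 = +0.053 to +0.707, or 2.4-fold (1.13 to 5.1). For S9, 0.036 / 0.167 = 0.216 and P = 0.83, as stated.

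**2. Size of a pure yield artefact.** One million children were simulated with no link between virus and pneumococcus. A shared log10 yield term was added to density and to each of three strains, and high shedding was classed by the S8 rule. Assumptions, none given in the documents:
- true virus SD 0.75 to 2.0 log10;
- strain positivity 30%, 45% and 50%;
- between-strain correlation 0.3;
- density SD 1.1 to 1.2 log10. The S8 standard error implies 0.94 to 1.22 for n = 150 to 213 and 50 to 70% high shedders; for example 0.167 × √(213 × 0.5 × 0.5) = 1.22.

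| Yield SD (log10) | As a fold | Spurious difference (log10) |
|---|---|---|
| 0 | 1.0 | 0.00 |
| 0.2 | 1.6 | +0.04 to +0.10 |
| 0.3 | 2.0 | +0.09 to +0.21 |
| 0.4 | 2.5 | +0.15 to +0.35 |
| 0.5 | 3.2 | +0.23 to +0.50 |
| 0.6 | 4.0 | +0.32 to +0.67 |

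Interpolating, the lower confidence limit of +0.053 is reached at a yield SD of about 0.15 to 0.25 log10 (1.4- to 1.8-fold). The full +0.380 is reached at about 0.42 to 0.65 log10 (2.6- to 4.5-fold).

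As a cross-check, take one normal virus measure with total SD v, split at its median, and yield SD s. The spurious difference is 2√(2/π) × s²/v. With v = 1.0, s = 0.2 gives 0.064 and s = 0.5 gives 0.399, the same order as the simulation. Removing 0.064 leaves (0.380 − 0.064) / 0.167 = 1.89, P about 0.06.

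**3. Do S8 and S9 differ?** 0.380 − 0.036 = 0.344. If the estimates are independent, the SE is 0.167 × √2 = 0.236, z = 1.46 and P = 0.145. At a correlation of 0.25, P = 0.093; at 0.5, P = 0.039. The correlation is not reported.

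**4. The S9 cut-off.** Taken literally, day 2 samples are classed by a threshold from another visit. However, the shedding SE is 0.167 in both tables, and the other SEs agree within about 3% (0.170 and 0.172; 0.162 and 0.166; 0.257 and 0.260). This would fit a similar high/low split in both tables, and so a footnote carried over from S8.

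**The case against.** A reader might infer that the S8/S9 pair reveals the artefact: an association on the same swab and none across swabs. The documents do not support that. The two estimates have not been shown to differ, and a null day 2 result fits a real effect of concurrent viral load equally well. If the S9 cut-off is misplaced, its null is weaker evidence still.

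There is also evidence that a virus-density link need not depend on a shared swab. Respiratory virus at day 0, measured on a different swab from day 7 density, carries +0.442 (P = 0.0099) in S8 and +0.42 (P = 0.015) in S9. These are other viruses, so this is not proof, but it stands.

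The magnitudes rest on assumed SDs. The calculations also treat every child as a carrier. If S8 includes non-carriers, which it does not say, yield cannot move them; at the 80% carriage used in section 123, an artefact of 0.40 shrinks to about 0.8 × 0.40 = 0.32.

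The remedy is not neutral either. Total 16S or human-gene signal at day 7 is measured after vaccination, and the protocol itself expects LAIV to infect nasal epithelium and perhaps alter the microbiota. Adjustment could remove part of a real effect, so the adjusted model should not be a pass/fail test. Making S9 the lead analysis would change the question from concurrent load to early replication.

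Finally, laboratory procedures are not included in these documents, so the supportable wording is that no correction is stated. Section 97 gives no reason for its antibody ratio, so it cannot be read as an admission about swab yield.

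These objections limit the conclusion but leave the design problem in place: same swab, raw Ct, no stated yield term and no day 0 density.

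**Conclusion.** The point holds as a possible upward bias of unknown size. As specified, S8 cannot separate an effect of viral replication from variable sampling or from dense carriage before vaccination. Modest yield variation (about 0.15 to 0.25 log10 SD) would match the lower confidence limit, while substantial variation (about 0.42 to 0.65 log10 SD) would be needed to account for the whole +0.380. Both ranges depend on the assumptions listed above.

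Two stronger readings go too far. One is that swab yield produced the association, which would need a yield SD the documents do not give. The other is that S8 demonstrates a dose-response; the table is titled an association and its contrast is binary. S8 is a supplementary comparison among vaccinated children, and the randomised comparison of LAIV with control is unaffected.

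**What to change.** - **Main change:** refit S8 and S9 with day 0 pneumococcal density as a covariate. It is already measured and precedes vaccination. It addresses prior carriage but not day 7 swab yield.
- **Sensitivity analysis:** add a yield marker from the day 7 swab, either the planned 16S qPCR with pneumococcal copies subtracted or a human-gene PCR on existing extracts. Alternatively, use the planned relative abundance of the pneumococcal OTU. Show adjusted and unadjusted results side by side and state that these markers are post-vaccination.
- **Table S9:** define high day 2 shedding from the day 2 Ct distribution, or use Ct as a continuous variable. If the day 2 median was in fact used, correct the footnote.
- **Reporting:** give n for both tables, say whether non-carriers are included, and present S8 and S9 together. Describe S8 as a same-swab association open to a shared-sampling artefact, not as evidence of an effect of shedding.

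The cost is a re-analysis of collected data, or at most one extra PCR target. The downsides are slight loss of precision and possible over-adjustment in the sensitivity model.
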